### Study Procedures

#### Recruitment

We will select 800 current smokers and 400 users of iQOS with HeatStick based on the inclusion criteria. The recruitment strategy for smokers of combustible cigarettes and participants who use iQOS with HeatStick includes word-of-mouth communication to friends and spouses of individuals who participated in the cross-sectional study, advertisements, social media engagement (ie, Facebook, Instagram, WhatsApp chats), and outreach to community groups. In addition, we will recruit users of iQOS with HeatSticks at iQOS stores in Almaty, Kazakhstan.

To achieve comparability of comparison groups at baseline, the matched-pair cohort study design will be implemented, where a pair contains one iQOS with HeatSticks user and two conventional cigarette users. The following variables will be utilized for matching: gender, age (±3 years), education (as a proxy for socioeconomic status), and number of pack-year (±5 pack-years) as the baseline exposure level (number of pack-year).

Once potential participants who meet inclusion criteria are identified, they will undergo further medical assessment at the KAPM COPD Center to test for exclusion criteria and to start baseline comprehensive assessment.

The study will include (1) baseline comprehensive assessment at outset of the study during the enrollment period, which is expected to last for about 6 months (4^th^quarter of 2017 to 1^st^-3^rd^quarters of 2018); (2) annual comprehensive assessments at 2^nd^-4^th^quarters of 2018-2022; (3) periodic prospective case finding and exacerbation history assessment on quarterly basis (every 3 months), semiannual, and annual basis; and (4) continuous COPD case-finding activities based on patient self-assessment and professional clinical assessment during periodic visits to KAPM dedicated primary care unit.

**Table 1 table1:** Sample size calculations.

Primary confirmatory variable	Estimated value of outcome variable in exposure group	Estimated value of outcome variable in control group	Sample size exposed/ nonexposed	Adjusting sample size for anticipated dropouts
Symptomatic smokers defined by CAT ≥10	17%	42.8%	23/46	31/62
6MWT <450 m	11%	16.7%	260/520	347/694
Annual exacerbation rate	0.05	0.1	255/510	340/680

Baseline comprehensive assessment at outset of the study (4^th^quarter of 2017) and annual assessments (4^th^quarters of 2018-2020) will include the following:

COPD assessment test6MWTShort form-12 (SF-12) Quality of Life questionnairespirometry (forced expiratory volume in 1 second [FEV1]/ forced vital capacity [FVC] bronchodilation testECGbody mass indexCT scan of the chestCOPD-related conditions and comorbidities identified by using our proprietary mHealth technologies: SymptoMaster and MedintelStanford 25 comprehensive clinical assessment to identify clinical signs of COPD and comorbidities [20,21]laboratory testing for complete blood count (CBC), blood cholesterol level, high-density lipoproteins (HDL), low-density lipoproteins (LDL), triglycerides, C-reactive protein, fibrinogen, glucosebiomarker testing for sRAGE, ICAM1, CCL20, and probably other biomarkers (to be determined based on validity and feasibility of each test)

One important feature for an efficient support tool is the ability to detect any symptom that can lead to a potential new COPD case finding and exacerbation. We will administer the CAT to identify COPD symptoms and quantify them during a stable phase of disease (>6 weeks after any exacerbation). The CAT is a validated 8-question health-status instrument with scores ranging from 0-40, with higher scores indicating greater severity of symptoms. GOLD uses a CAT score ≥10 as a threshold for more severe symptoms in consideration of treatment regimens [7].

In the context of COPD, an exacerbation is defined as a worsening of a patient’s symptoms from their usual stable state. The symptoms can then be analyzed by physicians using SmartHealth algorithms to detect the potential risk of an exacerbation. We will obtain an exacerbation history prospectively (ie, every 3 months) with the use of a structured questionnaire. Exacerbations will be defined on the basis of the use of antibiotic agents, systemic glucocorticoids, or a combination of both or a health care utilization event (ie, office visit, hospital admission, or emergency department visit for a respiratory flare-up). Severe exacerbations will be defined as interactions that lead to hospitalization or an emergency department visit. Exacerbations will be managed by the participants’ primary care physicians in close communication with study participants, their families, and health care organizations in their service areas of Almaty.

The inclusion of secondary endpoints (eg, lab tests, ECG, and clinical assessment) allows for generating further hypotheses for different effects of switching to iQOS. Schedule of enrollment, data collection, and assessment are shown in Tables 2 and 3.

All study participants in both cohorts will receive smoking cessation advice according to clinical standards endorsed by Kazakhstan’s Health Ministry, offered throughout the study at each visit. The participants will also be offered formal professional assistance on smoking cessation. At the screening visit, in conjunction with signing the informed consent form, clinical investigators will give smoking cessation advice. It will be free of charge (paid by the sponsor) and is set out in the informed consent form. It will include psychological support to eliminate nicotine dependency, and participants will be referred to a specialist commercial medical organization in Almaty. We anticipate that some smokers and iQOS users will quit and that some smokers will switch to a reduced-risk product during the study. Quitting and switching will not be considered as reasons for early withdrawal and will be accounted for in sample size calculations.

#### Spirometry

Spirometry data will be collected using the combined spirometry system, BTL-08 SPIRO. All spirometry studies will be reviewed centrally to ensure quality control. Bronchodilator responsiveness will be considered positive if the subject had a ≥12% change in FEV1 or FVC above pre-bronchodilator measurements [22].

Each spirometer to be used in this study will be tested and continuously standardized with a 3.0-liter syringe. Each clinical coordinator will be certified after spirometry training. Quality assessments will be made on each study.

Smokers will be categorized for analysis using the GOLD staging system according to the results on spirometry, which will be performed before and after two inhalations of salbutamol, 0.1 μg per inhalation. Among the criteria needed to make a diagnosis of COPD are deficits in the rate at which one can forcefully exhale. Most experts consider a low ratio (<0.70) of the FEV1 to the FVC after bronchodilator use to be a key diagnostic criterion [7].

Once the diagnosis of COPD has been established, the GOLD nomenclature grades severity according to the degree to which the measured FEV1 is lower than the patient’s predicted value [7]:

GOLD stage 1 (mild disease): FEV1 ≥80% of the predicted valueGOLD stage 2 (moderate disease): FEV1 ≥50% and <80% of the predicted valueGOLD stage 3 (severe disease): FEV1 ≥30% and <50% of the predicted valueGOLD stage 4 (very severe disease): FEV1 <30% of the predicted value

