**Conclusions:**

This is the first cohort observational study in Kazakhstan to assess differences in lung function between users of the heated tobacco product, iQOS with HeatSticks, and smokers of conventional combustible cigarettes. The study results will add to knowledge on whether switching from combustible cigarettes to iQOS with HeatSticks affects respiratory symptoms and diseases, including the development and progression of COPD.

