## Introduction

Chronic obstructive pulmonary disease (COPD), the fourth leading cause of death in Kazakhstan, is a global public health problem. It is the third leading cause of death globally, accounting for 3.2 million deaths worldwide in 2015 [1]. In Kazakhstan, an expected 1.4 million people may have COPD based on estimations from neighboring countries [2]. COPD negatively affects the quality of life and is a major health care burden [3]. It is the third leading cause of hospital readmission within 30 days [4]. Cigarette smoke is the most common risk factor for COPD [5]. COPD is traditionally defined by airflow obstruction and includes emphysema, gas trapping, and chronic bronchitis [6]. Systemic effects (eg, on heart and muscles) and associated comorbidities (eg, heart failure, metabolic disorders, sleep apnea syndrome, and depression) may complicate the course of disease, posing challenges in the management of COPD [7-9].

Recently, we conducted a cross-sectional study of COPD among men and women aged 40-59 who currently smoke cigarettes, do not smoke, and stopped smoking 1-5 years ago [10]. We demonstrated that based on the COPD Assessment Test (CAT), respiratory symptoms are common in current smokers who have spirometric values that are generally considered to be within the normal range. We identified a relatively low percentage of participants with obstructed respiratory functions on spirometry. It was higher among current smokers (5.5%) compared to former and nonsmokers (3% among both groups). We found that 42% of current smokers had COPD symptoms based on a CAT score of ≥10—a prevalence of symptoms that was far greater than that among former smokers and controls who never smoked (17% and 12.5%, respectively). In addition, smoking cessation significantly reduced functional exercise incapacity, that is, inability to walk 450 meters within 6 minutes in the 6-Minute Walk Test (6MWT; 11% among ex-smokers compared to 16.7 % among current smokers).

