## Methods

### Study Design

The goal of this study is to evaluate whether the presence of respiratory symptoms, functional exercise incapacity, and COPD exacerbation rate across time are the same between the exposure group (users of iQOS with HeatSticks) and the control group (smokers of combustible cigarettes) through hypothesis testing.

In addition to this confirmatory goal, we would like to explore trends in spirometry results, chest CT scan results, prevalence of impaired quality of life, metabolic syndrome, abnormalities found by electrocardiography (ECG), physical exams, and serum lab tests among those who use iQOS with HeatSticks and those who currently smoke combustible cigarettes.

Exacerbation history will be collected prospectively (every 3 months) with the use of the adapted version of our proprietary SymptoMaster (Web, iOS, and Android) [16], and Medintel (Web) apps [17]. Symptoms history will be analyzed by clinical investigators. Should there be symptoms identified that are relevant to COPD, clinical investigators will approach health care organizations (serving participants in primary health care catchment area) to obtain ambulatory records of the use of antibiotics and/or systemic glucocorticoids or a health care utilization event.

Our primary confirmatory outcome variables are (1) presence of respiratory symptoms defined by CAT≥10, (2) functional exercise incapacity, and (3) exacerbation rate. The main exposure variable is smoking status (users of combustible cigarettes and users of iQOS with HeatSticks). The study groups are defined as:

Individuals (men and women) aged 40-59 years (inclusive) with a minimum of 10 pack-year smoking history who switched to and predominantly use the heated tobacco product iQOS with HeatSticks (exposure group). Predominant use of iQOS with HeatSticks is defined as >70% use.Individuals (men and women) aged 40-59 years (inclusive) who are currently smoking combustible cigarettes with a minimum of 10 pack-year smoking history (control group)

Pack-years will be calculated by taking the average number of cigarettes smoked per day divided by 20 and multiplied by the number of years smoked.

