As a result, the sample size of 1041 respondents is enough to detect significant differences in three primary confirmatory outcomes with at least 80% power. However, in addition to dropouts, we need to consider that participants may switch from one tobacco product to another, quit smoking, use several tobacco products at the same time, and the fact that a nonrandomized observational study needs to be adjusted for confounding factors. Even if most of these events do not cause subjects’ withdrawal, they lead to a decreased number of participants for further statistical analysis. Therefore, we need more participants to solve this issue. We propose recruiting 400 participants in the exposure (iQOS) cohort and 800 participants in the control (combustible cigarettes) cohort. The following sample size should allow us to achieve the confirmatory goal of the study: (1) iQOS with HeatSticks smokers (exposure group, N=400) and (2) conventional cigarette smokers (control group, N=800; total sample size=1200).

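### GOLD stage, the only spirometry severity scale the article names for analysis, would apply to about 66 of 1200 participants; FEV1 and FEV1/FVC should be named as continuous outcomes for the cohort comparison

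*Protocol article*

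**What the plan says.** The Spirometry section states: "Smokers will be categorized for analysis using the GOLD staging system according to the results on spirometry". It then gives the diagnostic threshold: "Most experts consider a low ratio (<0.70) of the FEV1 to the FVC after bronchodilator use to be a key diagnostic criterion". The four stages follow from FEV1 as a percentage of predicted, and they come into play only after diagnosis: "Once the diagnosis of COPD has been established, the GOLD nomenclature grades severity". No category is listed for a smoker without obstruction. The only other spirometry rule in that section is a cut of at least 12% for bronchodilator response.

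The Introduction describes the group's earlier "cross-sectional study of COPD among men and women aged 40-59 who currently smoke cigarettes" (former smokers and nonsmokers were also included) and says of obstruction on spirometry: "It was higher among current smokers (5.5%) compared to former and nonsmokers (3% among both groups".

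Study Design places spirometry among the exploratory items, where trends are to be examined; no scale is given. Tables 2 and 3 schedule FVC, FEV1, FEV1/FVC, FEF 25-75 and MEF at baseline and at the annual assessments. The abstract's conclusions nevertheless describe the study as the first in the country to "assess differences in lung function between users of the heated tobacco product, iQOS with HeatSticks, and smokers of conventional combustible cigarettes". The Discussion adds that it will settle whether switching reduces the development and progression of COPD, on the evidence of CT and spirometry.

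**The concern.** A severity scale built for diagnosed COPD is named for analysis in a cohort that, on the authors' own earlier data, is almost entirely unobstructed. On that scale, an unobstructed participant whose FEV1 falls during follow-up, but whose ratio stays at or above 0.70, shows no change at all. A comparison made this way would turn on a few dozen participants and on small movements across one threshold. It would give no estimate of the difference in FEV1 decline.

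At stake is how the lung-function result is read. A null finding on GOLD stage could be reported as no difference in lung function when the scale had little chance of showing one. The abstract and the Discussion both give lung function or COPD progression more weight than an exploratory listing would suggest.

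**Working it through.** The article gives no sample size or power for spirometry, so there is no figure of that kind to reproduce.

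**Inputs from the article**
- Obstruction 5.5% in current smokers, 3% in former smokers (Introduction).
- Cohorts of 400 and 800, total 1200 (Sample Size Calculation: "iQOS with HeatSticks smokers (exposure group, N=400"; controls are twice that).
- Dropout of 10% a year (Sample Size Calculation).

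**Step 1: how many would hold a stage**
- Exposure cohort: 400 × 0.055 = 22. Control cohort: 800 × 0.055 = 44. Total 66.
- Unstaged: 1200 − 66 = 1134, or 94.5%.
- With 10% yearly dropout and unchanged prevalence: 66 × 0.9^4 ≈ 43 after four years and 66 × 0.9^5 ≈ 39 after five, spread over up to four stages.

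**Step 2: information kept by a cut**

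For a normally distributed measure cut at prevalence p, the efficiency relative to comparing means is φ(z_p)² / [p(1 − p)].

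| Obstructed share p | Information kept |
|---|---|
| 3% | 16% |
| 5.5% | 24% (0.238) |
| 10% | 34% |
| 20% | 49% |

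Only 5.5% and 3% are the article's figures; 10% and 20% are assumed, to show the range.

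Power after the cut is Φ[(1.96 + z_power) × √efficiency − 1.96]. Where the continuous analysis has 80% power at two-sided 0.05, this is Φ[(1.96 + 0.842) × √0.238 − 1.96] = Φ(−0.59), about 28%.

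**Step 3: an illustration using the article's two prevalences**

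Suppose the exposure cohort resembled former smokers (3%) and the controls current smokers (5.5%). This borrows the analogy the article uses to size its primary outcomes; it makes no such assumption for spirometry. On a normal scale the implied shift is 1.881 − 1.598 = 0.283 SD.

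- Continuous, 400 v 800: Φ[0.283 / √(1/400 + 1/800) − 1.96] ≈ 99.6%. With 236 v 472, the numbers left after five years of 10% dropout, about 94%.
- Obstructed versus unobstructed, 400 v 800: the pooled proportion is (12 + 44)/1200 = 0.0467, the pooled SE 0.0129 and the unpooled SE 0.0117. Power is Φ[(0.025 − 1.96 × 0.0129)/0.0117] ≈ 49%. With 236 v 472, about 30%.
- Reaching 80% power on the binary scale at 0.05 would need about 793 v 1586.

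**The case against.** The strongest reply is that no passage makes GOLD stage the sole spirometry analysis. The Spirometry sentence classifies people, which fits a descriptive table or subgrouping as well as an outcome. Study Design speaks of trends in spirometry results and uses the word prevalence for other items in the same list. The Statistical Analysis section plans means, medians and individual trajectory plots, and applies GEE and mixed models to outcome variables generally. FEF 25-75 and MEF are scheduled although staging does not need them. Spirometry is exploratory, and this is a condensed article whose analysis plan is not shown.

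Most of this stands. A reader might infer that the plan discards continuous FEV1 and FEV1/FVC, or that most participants' lung-function data would not count. The documents do not support that; every loss figure above is conditional on a stage-based or obstructed/unobstructed comparison. Nor would such a comparison rest on staged participants alone, because unobstructed participants could serve as the reference category. In that case, however, the outcome is essentially the cut evaluated in steps 2 and 3.

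The reply does not remove the point. The trends wording names no scale, whereas the Spirometry section does. Scheduling a measurement does not settle how it will be analysed.

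A reader might also extend the argument to the quality-of-life questionnaire, since Study Design lists "prevalence of impaired quality of life, metabolic syndrome". The article gives no scoring, cut-off or model for it and does not exclude analysis of the score, so no claim is made here.

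**Conclusion.** The point holds as a conditional weakness in an exploratory analysis. The spirometry severity scale named for analysis suits this population poorly: at 5.5% obstructed, about 66 of 1200 would hold a stage. A cohort comparison on that scale would keep roughly a quarter of the information in a normal measure. Even at 20% obstructed it would keep only about half. This is too little to carry the statements on lung function and COPD progression in the abstract and Discussion. The three confirmatory outcomes and their tests are unaffected.

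The size rests on these assumptions:
- A normally distributed measure, a common shift and a single cut. GOLD uses the ratio first and then FEV1 percent predicted, so the figures approximate the loss.
- The 5.5% is cross-sectional, from current smokers with no stated pack-year minimum. The requirement of at least 10 pack-years and the years of follow-up could raise the share. The exclusion for a history of chronic lung disease could lower it at baseline if read to include COPD.
- The 3% v 5.5% contrast is an illustration, not an effect the article assumes for spirometry.

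**What to change.** In the Spirometry section, state that post-bronchodilator FEV1 and FEV1/FVC are compared between the cohorts as continuous repeated measures. Use the time-by-group GEE or mixed-model framework already described under Statistical Analysis, adjusted for age, sex, height and baseline pack-years. Keep GOLD stage as a descriptive table and add an explicit unobstructed category so that every participant is classified.

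The cost is a change of wording and one additional model per measure. Spirometry and height are already collected, and because the outcome is exploratory the confirmatory significance level is untouched. Differences in FEV1 decline may be less familiar to some readers than stages; the descriptive table covers that. If continuous models are already intended, the edit only makes this explicit.

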#### Assessment Test for Chronic Obstructive Pulmonary Disease

The CAT is a validated, short (8-item) questionnaire to be completed by study participants. Despite the fact that CAT is designed for patients with COPD, it can be used to measure respiratory symptoms among all participants including those who have preserved pulmonary function [10]. The CAT has a scoring range of 0-40, with the cut-off point equaling 10.

**Table 2 table2:** Schedule of participants enrollment and baseline assessment, 2017-2018.

Test	Screening^a^	Baseline visit^b^
Informed consent process	X	
Review inclusion/exclusion criteria to determine study eligibility, including smoking status and iQOS use	X	
Review medical history	X	
Provide study requirements handout (explain study/visit requirements)	X	
Pregnancy test	X	X
Stanford 25 comprehensive clinical assessment		X
Spirometry (FVC^c^, FEV^d^, FEV1^e^, FEV1/ FVC, FEF^f^ 25-75, MEF^g^), bronchodilation test using salbutamol		X
CAT^h^		X
6MWT^i^		X
Short form-12 Quality of Life questionnaire		X
ECG^j^		X
Body mass index		X
Smoking status and exposures		X
Comprehensive physical assessment Stanford 25		X
Previous COPD^k^ exacerbations based on use of inhaled steroids, antibiotics, inhaled bronchodilators, steroids		X
Previous COPD exacerbations based on health care visits (office visits, admissions to emergency department or hospital)		X
Previous COPD severe exacerbations based on emergency department admission or hospitalizations		X
Laboratory testing for blood cholesterol level, CBC^l^ (25 parameters); HDL^m^, LDL^n^, triglycerides, C-reactive protein, fibrinogen, glucose, glycosylated hemoglobin		X
Biomarker testing for sRAGE^o^, ICAM1^p^, and CCL20^q^		X
Lung computer tomography		X

^a^Months –3 to 3.

^b^Months 0 to 3.

^c^FVC: forced vital capacity.

^d^FEV: forced expiratory volume.

^e^FEV1: forced expiratory volume in 1 second.

^f^FEF: forced expiratory flow.

^g^MEF: maximum expiratory flow.

^h^CAT: COPD Assessment Test.

^i^6MWT: 6-Minute Walk Test.

^j^ECG: electrocardiogram.

^k^COPD: chronic obstructive pulmonary disease.

^l^CBC: complete blood count.

^m^HDL: high-density lipoproteins.

^n^LDL: low-density lipoproteins.

^o^sRAGE:advanced glycosylation
end-product receptor.

^p^ICAM1: intercellular adhesion molecule 1.

^q^CCL20: macrophage inhibitory protein
3a.

**Table 3 table3:** Schedule of participants visits for data collection and monitoring, years 1-5.

Test	Year 1			Year 2				Year 3				Year 4				Year 5				
	Q^a^2	Q3	Q4	Q1	Q2	Q3	Q4	Q1	Q2	Q3	Q4	Q1	Q2	Q3	Q4	Q1	Q2	Q3		Q4
Stanford 25 comprehensive clinical assessment				X				X				X				X				
Spirometry (FVC^b^, FEV^c^, FEV1^d^, FEV1/ FVC, FEF^e^ 25-75, MEF^f^), bronchodilation test using salbutamol				X				X				X				X				
CAT^g^				X				X				X				X				
6MWT^g^				X				X				X				X				
Short form-12 Quality of Life questionnaire				X				X				X				X				
ECG^g^				X				X				X				X				
Body mass index				X				X				X				X				
Smoking status, exposures				X				X				X				X				
Laboratory testing for blood cholesterol level, CBC^j^ (25 parameters); HDL^k^, LDL^l^, triglycerides, C-reactive protein, fibrinogen, glucose, glycosylated hemoglobin				X				X				X				X				
Biomarker testing for sRAGE^m^, ICAM1^n^, and CCL20^o^				X				X				X				X				
Lung computer tomography				X				X				X				X				
Continuous health status monitoring, including home visits, phone, email, telemedicine, and COPD^p^ Center visits as necessary	X	X	X	X	X	X	X	X	X	X	X	X	X	X	X	X	X		X	X
Monitoring COPD exacerbations based on use of inhaled steroids, antibiotics, inhaled bronchodilators, steroids, health care visits (office visits, emergency department, or hospital)	X	X	X	X	X	X	X	X	X	X	X	X	X	X	X	X	X		X	X
Monitoring adverse events and serious adverse events using SymptoMaster self-assessment that triggers notification	X	X	X	X	X	X	X	X	X	X	X	X	X	X	X	X	X	X		X

^a^Q: quarter.

^b^FVC: forced vital capacity.

^c^FEV: forced expiratory volume.

^d^FEV1: forced expiratory volume in 1 second.

^e^FEF: forced expiratory flow.

^f^MEF: maximum expiratory flow.

^g^CAT: COPD Assessment Test.

^h^6MWT: 6-Minute Walk Test.

^i^ECG: electrocardiogram.

^j^CBC: complete blood count.

^k^HDL: high-density lipoproteins.

^l^LDL: low-density lipoproteins.

^m^sRAGE: advanced glycosylation
end-product receptor.

^n^ICAM1: intercellular adhesion molecule 1.

^o^CCL20: macrophage inhibitory protein
3a.

^p^COPD: chronic obstructive pulmonary disease.

